## Concomitant Therapy

For this protocol, participants engage in other treatments and there are no restrictions on medications. Psychotropic medication usage will be assessed at each assessment time point and documented in the relevant Medication Compliance Questionnaire, and any psychosocial interventions will be tracked using the Treatment History Interview.

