# STUDY ASSESSMENTS AND PROCEDURES

## Endpoint and Other Non-Safety Assessments

Please refer to Section 1.3, Schedule of Activities to see list of assessments, assessment modality, and timetable of specific administrations. Of note, guardians will be mainly reporting on adolescent thoughts, feelings, and behaviors for the assessment areas described below.

Demographics and Background Variables. Routine demographic variables will be collected. We will ask questions from the overview of the *Kiddie Schedule for Affective Disorders and Schizophrenia – Present and Lifetime version (KSADS-PL*)(52) to assess for current living situation, legal involvement, history of abuse, family psychiatric history, treatment history and payor information. Self-report forms will be used to ask about sexual and gender identity.

Suicidal Events. Suicidal events (operationalized as a composite score of suicide attempts and inpatient hospital/ED admissions)(42) will be assessed with the *Columbia-Suicide Severity Rating Scale* (50) and the *Child and Adolescent Services Assessment* (53). The C-SSRS assesses the range of suicidal behavior including preparatory acts, aborted attempt and interrupted attempt, and passive and active SI, as well as intensity of ideation. At f/u, suicidality since the last assessment and in the prior week will be assessed. The CASA is a semi-structured interview that obtains information about service use across multiple sectors (e.g., juvenile justices, schools). Adequate reliability has been demonstrated for this measure (ICCs=.74-.76)(53). Interviews will be administered at baseline, 3-, 6-, and 12-months f/u, with the 6-month follow-up as our primary outcome (Ho1A). The CASA will be used to systematically assess ED evaluations and psychiatric hospitalizations.

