handled with multiple imputations, with assumptions checked with sensitivity analyses (76), is pre-specified (as are all aspects of our analysis plan). We will adhere to intent-to-treat principles, and all aspects of data analysis will be pre-specified as reflected in this proposal, and with modification following proposal review and discussions with program and our Data Safety and Monitoring Board. Preliminary analyses will include descriptive statistics to examine the distributional and psychometric properties of the variables (e.g., normality, internal consistency). Variables will be transformed to better approximate normality if this is necessary given the observed distribution and the assumptions of the analysis model. We will also examine post-inclusion attrition by comparing study completers to dropouts on sociodemographic, baseline data, and psychotropic medication usage to determine if they differ systematically. We will examine the success of the stratified randomization by examining between-group differences at baseline. Preliminary analyses may also include analyses of adverse events, the progress of recruitment and retention, and data processing and quality markers as the study progresses. Daily mood monitoring data is not included in outcome analyses because it is conceptualized as part of this adjunctive intervention and only collected in one condition.

Missing data. To accommodate attrition and other sources of missingness, we will utilize the method of multiple imputation by chained equations. At least 50 replicates of each missing value will be generated for inclusion in analyses. This method can accommodate clustering of repeated measures at the level of the. We have previously used these methods in successful analyses of trials of exercise interventions.

Statistical computing. Modeling will be performed using Stata (Stata Corp, College Station, TX, version 16.2 or higher) and R software (R Foundation for Statistical Computing, Vienna, Austria, version 4.0 or higher) and Mplus (version 8.4 or higher, Muthen & Muthen, Los Angeles, CA). Analyses and reporting will be executed and archived to ensure full replicability and reproducibility by analysts at Brown University, under the direction of the project methodologist, [name].

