**Aim 1A-C:** *Examine the effectiveness of STEP in reducing suicidal events, active SI*, *and depression at 3- and 6-month follow-up (f/u).* We hypothesize that those randomized to STEP, compared to ETAU, will have (**H1A**) lower prevalence of suicidal events (operationalized as either a suicide attempt or emergency intervention to intercede when there is a high likelihood of an attempt) **(H1B**) lower prevalence of time with active SI (operationalized as SI with intent or plan), and (**H1C**) lower level of depressive symptoms, over the 6-month follow-up period. Aim 1 analyses will use a repeated measures design and a multilevel or mixed effect modeling framework. For H1A and H1B, the outcome is binary and a mixed effect logistic regression model will be used. For H1C, the outcome is continuous and a mixed effect general linear model will be used. For H1B, the outcomes are repeatedly observed over follow-up weeks within the 6M timeframe (24 weeks), and can yield a categorical (active SI, worst week) outcome, which would be analyzed like H1A or a continuous (proportion of weeks with active SI) outcome, which would be analyzed differently like H1C. For H1A and H1C the outcome is observed twice at the scheduled follow-ups (3M, 6M). For all hypotheses, we will treat the individual as the random effect. Treatment effects will be estimated as the weighted average of the differences between ETAU and STEP groups over all follow-up times, adjusting for follow-up time.

In secondary analyses to identify potential mechanisms (i.e. mediators) of treatment effectiveness that occur after randomization, we will repeat these analyses using medication use and psychosocial treatment as covariates.

In secondary analyses, payor data will be examined as a potential moderator or predictor of these outcomes.

In secondary analyses, the patterns of change in depressed mood (BDI scores) will be evaluated using random effects models for longitudinal data.

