**Aim 3**: *Examine whether hypothesized mechanisms mediate reduction of suicidal events and ideation*. **H3:** Treatment-related changes in attention to positive affect, gratitude, satisfaction with life, and attention to negative affect at 3M follow-up will be related to improvements in SE and SI at the 6M f/u. Analysis: Mediation will occur when the outcomes (SE, SI) and the putative mediators (PA, gratitude and satisfaction with life, NA) are correlated, and that the distribution of the mediators varies according to treatment (Aim 2). We will approach the analysis using the Baron & Kenney (77) approach to mediation, with modifications for non-normal dependent variables, which is similar to the principal stratification approach to causal mediation analysis (78). We will approach this analysis using a cross-lagged panel model and a path analysis framework. Specifically, we will regress 6M outcomes and mediators on 3M outcomes and 3M mediators, and evaluate the effect of 6M outcomes regressed on 3M mediators accounting for any residual correlation of 6M outcome and 6M mediators and the 3M correlation of outcomes and mediators. All outcomes and mediators at all time points are regressed on treatment condition. We will quantify the total effect of treatment assignment in 6M outcomes, and the indirect effect of treatment in 6M outcomes via M3 mediators. Following Mandolando and Greenland (79), we will infer meaningful level of mediation if at least 10% of the total effect of treatment in 6M outcomes is mediated via M3 mediators. We will characterize the precision and statistical significance of mediation effects using bootstrap methods for interval estimation (80). ***Sample size and statistical power considerations.*** We used Monte Carlo methods to identify conditions in which a 10% difference (or greater difference) in the main treatment effect is to be detected when comparing to a model adjusting for the putative mediator. Finding a mediation effect requires that the treatment group have a different distribution on the putative mediator (attention to positive affect, gratitude and satisfaction with life, attention to negative affect) and the mediator be related to the outcomes (SE, active SI). In plausible scenarios (a unit standard deviation difference on the mediator across treatment group), and a (polyserial) correlation of 0.3 or greater between the mediator and the outcome, we will have adequate (at least 88%) power to detect a 10% mediated effect of treatment group and the outcome (n = 162, 81 per group). Similarly, if the treatment produces a net half standard deviation difference in the mediator (reflecting a clinically meaningful change), and the mediator has a (polyserial) correlation of at least .25 with the outcome, we will have 83% power to detect the target mediated effect.

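### Adding post-randomization medication and psychosocial treatment as covariates to the Aim 1 models does not by itself show mediation, which is the purpose the protocol gives for it

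*Protocol*

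**What the plan says.** In Statistical Considerations, under Aim 1A-C, one sentence fixes both purpose and method. The purpose is given as "In secondary analyses to identify potential mechanisms (i.e. mediators) of treatment effectiveness that occur after randomization". The method is "we will repeat these analyses using medication use and psychosocial treatment as covariates". The analyses to be repeated are the mixed logistic models for suicidal events (H1A) and binary active ideation (H1B), and the mixed linear model for depression (H1C) or for the proportion of weeks with active ideation.

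The main estimate is defined separately, without these covariates: "Treatment effects will be estimated as the weighted average of the differences between ETAU and STEP groups over all follow-up times". The same chapter states "We will adhere to intent-to-treat principles".

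On how the covariates arise, Concomitant Therapy says "participants engage in other treatments and there are no restrictions on medications", and Known Potential Risks leaves participants free to have any treatment that is clinically indicated. On timing, Concomitant Therapy says "Psychotropic medication usage will be assessed at each assessment time point", and the Schedule of Activities puts the treatment and medication interviews at baseline, 3 and 6 months, alongside the outcomes.

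Aim 3 contains a fuller mediation model: 3-month mediators, 6-month outcomes, total and indirect effects, and bootstrap intervals. It covers positive affect, gratitude and life satisfaction, and negative affect. It does not cover medication or psychosocial treatment.

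**The concern.** A change in the treatment coefficient after adding a post-randomization variable is evidence of mediation only under conditions. The main one is that nothing else drives both that variable and the outcome. Here that is hard to believe. Treatment is given by indication, so a more severely ill adolescent is likely both to receive more of it and to do worse. Deterioration also feeds back into care: the protocol has the team contact the clinician if a participant worsens, and ideation with intent or plan triggers a clinician review. With covariate and outcome taken from the same interval, the order of the two is not fixed.

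For these two variables the stated method has no model of STEP on the mediator and no indirect effect. At stake is a false mechanism claim, or an adjusted coefficient misread as the effect of STEP.

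**Working it through.** The protocol gives no figure for this analysis, so there is none to reproduce. The check asks how far the STEP coefficient can move when the added variable is not a mediator.

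**Inputs from the protocol.** H1C effect 0.35 SD (the minimum detectable effect in the Aim 1 power paragraph). Event rates 38% and 17% (Aim 1D, stated for 12 months and used here only as an illustration). The 10% mediation rule (Aim 3).

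**Inputs assumed.** Unmeasured severity U acts on both treatment use M and outcome Y with path c = 0.3 or 0.5. STEP shifts M by a = 0.2, 0.3 or 0.5 SD in either direction. M has no effect on Y.

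**1. Linear model (H1C).** With M and Y scaled to unit variance within arm, their within-arm covariance is c². The coefficient on M is then c², and

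- unadjusted effect = −0.35
- adjusted effect = −0.35 − a·c²
- false mediated share = −a·c² / 0.35

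| a | c | a·c² | Adjusted effect | False share |
|---|---|---|---|---|
| −0.2 | 0.3 | −0.018 | −0.332 | 5.1% |
| −0.2 | 0.5 | −0.050 | −0.300 | 14.3% |
| −0.3 | 0.3 | −0.027 | −0.323 | 7.7% |
| −0.3 | 0.5 | −0.075 | −0.275 | 21.4% |
| −0.5 | 0.3 | −0.045 | −0.305 | 12.9% |
| −0.5 | 0.5 | −0.125 | −0.225 | 35.7% |

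If STEP raises use, the effect grows by the same percentages. For a = +0.3 the adjusted effects are −0.377 and −0.425. Simulation with 1,000,000 records gave 7.8%, 21.5%, 12.9% and 35.6% for the four rows with a = −0.3 and −0.5, and −7.8%, −21.8%, −13.0% and −36.2% for the mirror cases.

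**2. When the linear comparison is sound.** If a = 0, adjusted and unadjusted effects are equal. If M is a true mediator without confounding (STEP to M −0.5, M to Y 0.2, direct effect −0.25), the total is −0.25 + 0.2 × (−0.5) = −0.35 and the true share is 0.10/0.35 = 28.6%. Simulation gave a total of −0.347, an adjusted effect of −0.247 and a share of 28.8%.

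**3. Logistic model (H1A, binary H1B).** The unadjusted log odds ratio is ln(0.17/0.83) − ln(0.38/0.62) = −1.586 + 0.490 = −1.096. Simulated results:

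- M predicts Y but STEP does not affect M, so there is no mediation. The log odds ratio moves to −1.29, −1.49 or −1.73 for M coefficients of 1, 1.5 and 2, a change of 18%, 36% or 57% from non-collapsibility alone.
- Severity drives both (coefficient 1.0), STEP shifts the log odds of use by ∓0.5, and M has no effect on Y. The log odds ratio moves to −1.05 or −1.20, a change of 4% or 9%.
- M depends only on whether an event occurred. The log odds ratio does not change (−1.096 to −1.097).

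These logistic runs used one record per person and no random intercept. The planned mixed models already condition on the individual, which would absorb part of the non-collapsibility shift from stable differences between people. The percentages are therefore illustrations, not forecasts.

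**The case against.** The analysis is labelled secondary and looks only for potential mechanisms. Lagging, coding and baseline adjustment may be set out in a statistical analysis plan that is not at hand. That is fair, and those details are not the point. The point is that the protocol itself pairs a purpose with a method that does not deliver it.

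Several stronger readings are tempting, and the documents do not support them:

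- **A reader might infer that covariate adjustment can never identify a mediator.** In the linear model, comparing coefficients works when mediator and outcome share no confounder (step 2).
- **A reader might infer that the trial's treatment effect is biased.** The primary estimate does not include these covariates, and the protocol never says the adjusted coefficient will be reported as the effect of STEP. In the linear model there is also no distortion if STEP leaves treatment use unchanged, and no section says that STEP changes it.
- **A reader might apply the 10% rule here.** The sentence "we will infer meaningful level of mediation if at least 10% of the total effect of treatment in 6M outcomes is mediated" belongs to Aim 3 and its own mediators. Aim 1 sets no threshold, so 10% is only a benchmark.
- **A reader might infer that the covariate contains part of the outcome.** The H1A outcome is "operationalized as a composite score of suicide attempts and inpatient hospital/ED admissions", with service use taken from the Child and Adolescent Services Assessment. A screen version of that instrument is also listed under Ancillary Treatment, so overlap is possible. But Concomitant Therapy assigns the covariates to other instruments, and nothing says hospital or emergency care enters them.
- **A reader might rest the case on reverse causation.** On its own it left the log odds ratio unchanged in step 3.

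**Conclusion.** The point holds as a limited one. Refitting the Aim 1 models with these two covariates does not by itself show mediation, and the adjusted coefficient should not be read as the effect of STEP. In the linear case a variable with no effect on outcome produces a change of about 5% to 36%, and four of the six scenarios in the table exceed the 10% that Aim 3 would call meaningful. This rests on assumed severity paths of 0.3 to 0.5 and an assumed STEP shift in use of 0.2 to 0.5 SD. The absolute shift (0.018 to 0.125 SD) does not depend on the size of the STEP effect, so the false share would be larger if the true effect were below 0.35. In the logistic models the same confounding moved the log odds ratio less (4% to 9%), but non-collapsibility can move it with no mediation at all.

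**What to change.** Remove the mediator purpose from the covariate-adjusted Aim 1 models, and report medication use and psychosocial treatment by arm.

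If a mechanism analysis of these variables is wanted, extend the lagged Aim 3 model to them:

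- treatment use over 0-3 months as mediator and outcome over 3-6 months;
- a model of STEP on the mediator, and an indirect effect with a bootstrap interval;
- adjustment for baseline severity, the stratification factors (site, history of suicidal behavior, sexual or gender minority status) and baseline treatment use;
- emergency and inpatient care kept out of the mediator when the outcome is H1A;
- a sensitivity analysis for unmeasured confounding, and an exploratory label.

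The data are already scheduled for collection at baseline, 3 and 6 months. The cost is revised wording, a little more analysis work and a more modest mechanism claim.

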# PROTOCOL SUMMARY

## Synopsis

| **Title:** | Skills to Enhance Positivity in Adolescents at Risk for Suicide |
| --- | --- |
| **Grant Number:** | MH123556-01A1 |
| **Study Description:** | The purpose of this study is to examine the effectiveness of the Skills to Enhance Positivity (STEP) intervention in reducing suicidal behaviors in adolescents who have been admitted to an inpatient psychiatric unit due to suicide risk. |
| **Objectives:** | Primary Objective: Examine the effectiveness of STEP in reducing suicidal events (suicide attempt or emergency intervention to intercede attempt), active SI (with intent or plan), and depression at 6-month follow-up (primary endpoint outcomes) and suicidal events at 12-month follow-up (distal, endpoint outcome).  Secondary Objective: Examine engagement of the hypothesized mechanisms (attention to positive and negative affect) at the 3- and 6-month follow-up.  Tertiary Objective: Examine whether hypothesized mechanisms mediate reduction of suicidal events and ideation. |
| **Endpoints:** | Primary Endpoint: Suicidal events, active suicidal ideation, and depression at 6 month follow-up.  Distal Primary Endpoint: Suicidal events at 12 month follow-up.  Secondary Endpoint: Attention to Positive Affect and Negative Affect at 6 month follow-up. |
| **Study Population:** | Adolescents, regardless of sex, gender, race, and ethnicity, between the ages of 12-18, who have been hospitalized due to suicide risk (i.e., a suicide attempt or suicidal ideation) will be recruited for study participation from three adolescent units at Boston Children’s Hospital (Boston, MA), Butler Hospital (Providence, RI), & Bradley Hospital (Providence, RI). Target recruitment is 216. |
|  |  |
| **Phase or Stage:** | Phase III |
| **Description of Sites/Facilities Enrolling Participants:** | Three sites, all in the United States, will be enrolling participants: 1) the adolescent inpatient unit at Boston Children’s Hospital; 2) the adolescent unit of Butler Hospital; and 3) the adolescent inpatient unit at Bradley Hospital |

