# STUDY DESIGN

## Overall Design

This is a randomized controlled trial (RCT) of Skills to Enhance Positivity (STEP) vs. Enhanced Treatment as Usual (ETAU). It is hypothesized that those randomized to STEP, compared to ETAU, will have lower rates of suicide events, active SI, and depression over the 6-month follow-up period (primary endpoint), and over 12 months of follow-up (secondary endpoint). Recruitment will occur at three sites, Boston Children’s Hospital, Butler Hospital, and Bradley Hospital. Eligible individuals who consent to participate will be randomly assigned to either STEP or ETAU in a 1:1 allocation after the baseline assessment. Co-I [name] will prepare a stratified [by study site, history of SB (yes/no), and sexual or gender minority (yes/no)} randomization schedule using random blocks and provide this to our REDCap administrator; study staff will not have access to randomization tables). Research staff will be able to obtain assignments in real time once consent and stratification variable information are recorded. We use random block sizes to prevent guessing of pending treatment assignments.

The study intervention, Skills to Enhance Positivity (STEP), is an adjunctive psychosocial intervention that involves 4 in-person sessions during a participant’s inpatient admission, followed by three months of text or email messaging for mood monitoring and skills delivery. (If participant has a shorter length of stay or is discharging early, the STEP sessions may be shortened so that the intervention can be delivered prior to discharge). The sessions and skills delivered via the text or email messages focus on the functions of positive affect and ways to bring greater attention to and awareness of positive emotions and experiences on a daily basis. Four videos with content derived directly from the treatment manual will be used to support the delivery of the STEP skills that are covered in the in-person sessions.

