Suicidal Ideation. Active SI will also be assessed using the C-SSRS; specifically, we will assess active SI, operationalized by a score of 3 or higher on the suicide ideation questions of C-SSRS, using their highest level of ideation during the worst week of the f/u interval. We will also obtain weekly ratings of SI using the methodology of the *Longitudinal Interval Follow-Up Evaluation* (LIFE)(54), at the 3-, 6-, and 12 month f/u’s. The LIFE format asks participants to rate their level of SI in the preceding interval on a 6-point psychiatric status rating (PSR) scale. This methodology, which yields weekly scores, as applied to the assessment of SI in adolescents has been successfully implemented in at least three NIMH-funded studies for which MPI [name] was a PI (K23MH069904, MH090137, MH059929). Our data from adolescents admitted to the Butler adolescent unit and followed for 6 months after discharge (K23MH069904) demonstrate a good range of variability in SI PSR scores (e.g., 20% clinically significant SI; 36% no weeks clinically significant SI, 6% chronic, unremitting, high levels of SI for all weeks of f/u). We will also administer the Suicide Ideation Questionnaire, a 30-item self-report instrument with good psychometric properties in adolescents.

Diagnostic / Symptom Rating Scales. Depression will be assessed by the *Beck Depression Inventory (BDI-II)* (39) administered to both adolescent and parent (about teen). The BDI-II is a widely used 21-item measure with excellent psychometric properties (55), and also validated in Spanish. Cronbach’s α in the pilot sample was 0.90 in adolescents and 0.89 in adults. Alcohol use will be assessed using the Alcohol Use Disorder Identification Test (AUDIT) and drug use will be assessed using the Drug Use Disorder Identification Test (DUDIT). Other symptom rating scales include the Borderline Evaluation of Severity Over Time (BEST) and the Columbia Impairment Scale (CIS). All are self-reports and assessments will be administered at baseline, 3-, 6-, and 12-months f/u.

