***Sample size and statistical power considerations:*** We determined minimal detectable effect sizes using Monte Carlo methods. This involved generating 1,001 simulated data sets representing our hypothesized effects, and our assumptions of a 10% loss by 3M and another 10% loss by 6M follow-up. We assumed repeated measures of depressive symptoms and the propensity to active suicidal ideation and suicidal events were all correlated at *r* = .5. Across the simulated data sets, we compute power as the proportion of replicates returning a significant effect in the hypothesized direction. Results of these models are summarized in Table 3, above. We summarize effects in terms of Cohen’s effect size statistics for clear expression of the minimum detectable effects. For H1A, H1B, and H1C, we will have sufficient power to detect small-to-medium effect sizes (.46, .31, .35, respectively).

**Aim 1D:** *Examine the effectiveness of STEP in reducing suicidal events at the 12-month f/u.* We hypothesize that those randomized to STEP, compared to ETAU, will have lower rates of suicidal events at the 12-month, long term f/u. This hypothesis will be tested to evaluate the durability of STEP effects over long-term follow-up. We expect to see the full effect of STEP at the 6M follow-up. This hypothesis will be evaluated with logistic regression, and not as part of the repeated measures analysis specified in H1A. If the effect continues through 12M, we will have 80% power to detect a difference in event rates of 38% ETAU and 17% STEP at the 12M follow-up.

In secondary analyses, the within-person frequency of suicidal events and suicidal ideation will be analyzed. These analyses will use (zero inflated) negative binomial regression models to account for the anticipated extreme skew of these outcomes.

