***Sample size and statistical power considerations***. The power to test the difference between two proportions, .17 and .38, is significantly different from zero can be found from POWER = F(sqrt(((n*(p1-p2)^2)/(p0*(1-p0)))/2) – F’(1-(a/2))), where F is the cumulative normal density function and F’ is the normal quantile function, a is the desired type-I error level, n is the per-group sample size and p1 and p2 are the target proportions. H1A and H1D have similar minimum detectable effect sizes because we use a conservative estimate of the within-person correlation of propensity to suicide for aims H1A-H1C. We conservatively use 162 as our sample size for these calculations but we expect to have a larger sample with suicidal event data because these data can be drawn from the electronic health record in addition to participant self-report.

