**Aim 2:** *Examine engagement of the hypothesized mechanisms at the 3- and 6-month f/u.* We hypothesize that those randomized to STEP, compared to ETAU, will have*:* **H2A:** higher attention to positive affect, assessed by implicit tasks; **H2B**: Increased gratitude and satisfaction with life, assessed by self-report; **H2C**: lower attention to negative affect, assessed by implicit tasks and self-report. Aim 2 analyses will use a repeated measures design and a multilevel or mixed effect modeling framework. For H2A, H2B, and H2C, the outcomes are continuous and a mixed effect general linear model will be used. Outcomes are repeatedly observed over follow-up and assessed at the scheduled follow-up (3M, 6M). For all hypotheses, we will treat the individual as the random effect. Treatment effects will be estimated as the weighted average of the differences between ETAU and STEP groups overall follow-up times, adjusting for follow-up time. ***Sample size and statistical power considerations***: As with H1, we determined minimal detectable effect sizes using Monte Carlo methods. This involved generating 1,001 simulated data sets representing our hypothesized effects, and our assumptions of a 10% loss by 3M and another 10% loss by 6M follow-up. We assumed repeated measures of the measures assessing the mechanisms (attention to positive affect, gratitude and satisfaction with life, and attention to negative affect) to have a stronger correlation within a respondent over time than the Aim 1 outcomes, and assumed *r* = .75, which results in a smaller effective sample size. Across the simulated data sets, we compute power as the proportion of replicates returning a significant effect in the hypothesized direction. Results of these models are summarized in Table 3, above. We summarize effects in terms of Cohen’s effect size statistics for clear expression of the minimum detectable effects. For Aim 2 outcomes, we will have sufficient power to detect small-to-medium effect sizes (*d* = .39).

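### H1B's detectable effect of .31 rests on a within-person correlation of .5 for weekly suicidal ideation that is called conservative but is not shown to be, and the protocol's own weekly data point higher

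*Protocol*

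**What the plan says.** Protocol Section 9, Aim 1A-C, sets one correlation for all three Aim 1 outcomes: "We assumed repeated measures of depressive symptoms and the propensity to active suicidal ideation and suicidal events were all correlated at" r = .5. It reports detectable effects of .46, .31 and .35 for H1A, H1B and H1C. H1A and H1C are observed twice, at 3 and 6 months. H1B is observed weekly over 24 weeks.

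The Aim 1D sample-size paragraph explains why H1A and H1D have similar detectable effects by saying that "we use a conservative estimate of the within-person correlation of propensity to suicide for aims H1A-H1C". The Aim 2 paragraph uses r = .75 and says that this stronger correlation is one "which results in a smaller effective sample size".

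Section 8.1, under Suicidal Ideation, describes six months of weekly SI ratings from an earlier cohort at the Butler adolescent unit. Among the examples it gives are "36% no weeks clinically significant SI, 6% chronic, unremitting, high levels of SI for all weeks of f/u". Section 9 does not link these data to the choice of .5.

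**The concern.** H1B has the smallest detectable effect of the three primary hypotheses because it averages 24 ratings per person. How much those ratings add depends almost entirely on how strongly they are correlated within a person. If the correlation is high, 24 weeks carry little more information than a few visits.

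The protocol gives ratings one week apart the same correlation as measures three months apart, and labels that value conservative. The treatment effect here is averaged over follow-up, so a larger r costs power, as the Aim 2 text recognises. A conservative value would therefore be a high one. The only weekly SI data in the document suggest that .5 is low on the propensity scale that Section 9 names. If so, H1B is less sensitive than stated.

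**Working it through.** **Inputs.** From the protocol: "Target recruitment is 216" with 1:1 allocation, so 108 per arm; "our assumptions of a 10% loss by 3M and another 10% loss by 6M follow-up", so 108 × .9 = 97.2 and 108 × .8 = 86.4 per arm; m = 24 weeks; r = .5; detectable effect .31. Assumed: 80% power for H1B (the text says only that power is sufficient) and two-sided 5% (no alpha is given, though the Aim 1D formula uses a/2).

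**Step 1: reproduce .31.** The variance of a person's mean over m equally correlated ratings, in SD² units, is V = (1 + (m − 1)r)/m. The detectable effect is 2.802 × √(2V/n).
- r = .5: V = (1 + 23 × .5)/24 = .521.
- n = 86.4: √(2 × .521/86.4) = .1098, and 2.802 × .1098 = .308. The stated .31 is reproduced.

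**Step 2: does .5 fit the Section 8.1 data?** Take a random-intercept probit model: SI is present in a week when a normal propensity with between-week correlation r exceeds a threshold set by weekly prevalence p. Integrate over the intercept to get the share of people with no SI weeks and with SI in all 24 weeks.

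| Setting | No weeks | All weeks |
| --- | --- | --- |
| Reported in Section 8.1 | 36% | 6% |
| r = .5, p = 20% | 25% | 0.2% |
| r = .5, p = 30% | 14% | 0.8% |
| r = .5, p chosen to give 36% none | 36% | 0.08% |

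No prevalence makes r = .5 match both figures. Fitting both gives r = .795 with p = 29% (r = .80 with 26 weeks). Section 8.1 also mentions 20% with clinically significant SI, without saying whether that counts weeks or people. If it is weekly prevalence and is held fixed, the 36% alone gives r = .65 and the 6% alone gives r = .89.

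**Step 3: power at .31, closed form.** Power = Φ(.31/√(2V/n) − 1.96).

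| r | V | Power, n = 86.4 | Power, n = 97.2 | Detectable effect, n = 86.4 / 97.2 |
| --- | --- | --- | --- | --- |
| .50 | .521 | 80.6% | 85.0% | .308 / .290 |
| .57 | .588 | 75.7% | 80.5% | .327 / .308 |
| .65 | .665 | 70.5% | 75.5% | .347 / .328 |
| .80 | .808 | 62.0% | 67.1% | .383 / .361 |
| .89 | .895 | 57.7% | 62.7% | .403 / .380 |

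**Step 4: power at .31, simulated yes/no weekly outcome.** Here r and the .31 shift act on the propensity scale. Each arm has 86 people with 24 weeks and 11 with 12 weeks, and the arms are compared on proportion of weeks with SI. For weekly prevalence of 25%, 30% and 40%:
- r = .5: 75%, 78%, 79%
- r = .65: 61%, 65%, 68%
- r = .8: 52%, 53%, 58%
- r = .89: 42%, 45%, 50%

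**Step 5: the other scale.** At the two-figure fit, the correlation of the observed weekly yes/no values is about .57. If r in Section 9 means that correlation, the .57 row of Step 3 applies: 80.6% falls to 75.7%, and 85.0% to 80.5%, about 5 points.

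**The case against.** The strongest reply is that nothing is miscalculated and that the higher correlation comes from a model, since the protocol prints no such value. This is right, and several parts of it stand:
- The fits assume one common correlation across all weeks. With serially correlated weekly errors added, the average latent correlation is about .74–.79 and closed-form power at .31 about 63–70%.
- The percentages are offered as examples of variability. They concern clinically significant SI in an earlier cohort at one unit, whereas H1B concerns SI with intent or plan at three hospitals. The threshold behind the 6% may also differ from that behind the 36%.
- On the yes/no scale, distribution-free bounds on the correlation run from .31 to .85, so on that scale the data do not exclude .5.
- The word conservative appears in a remark about why H1A and H1D are similar, although the sentence extends it to H1A-H1C.
- Section 9 also allows a worst-week categorical version of H1B, to which the 24-week calculation does not apply.

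A reader might infer that the sponsor's data establish r = .8 and that H1B's true power is only 50–67%. The document does not support that: .8 depends on the model and on a proxy, single-figure fits run from .65 to .89, and the yes/no reading costs little. Nor does it follow that .31 is an arithmetic error or that the trial is too small.

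What the reply does not remove is the direction. Section 9 speaks of propensity in both places, which favours the latent scale, and every fit on that scale exceeds .5.

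**Conclusion.** The point holds as a matter of an unsupported input. The value r = .5 for weekly SI is not shown to be conservative, the protocol's own reasoning makes a higher value the cautious one, and its quoted weekly data do not fit .5 on the scale it names. On that scale the plausible range is about .65 to .89, centred near .8. Power at .31 is then about 71–76% (closed form) or about 65% (simulated) at r = .65, and about 62–67% or 53–57% at r = .8, against about 80% as planned. On the yes/no scale the loss is about 5 points.

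These figures rest on an 80% target, two-sided 5%, an exchangeable correlation, and clinically significant SI standing in for active SI. Table 3 was not available to check. The stated sensitivity of a primary hypothesis should be re-examined; the design need not be.

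**What to change.** Estimate the week-to-week correlation from the existing weekly LIFE SI ratings, using the H1B definition of active SI as closely as those ratings allow. Rerun the H1B simulation at that value. Restate the H1B detectable effect in Section 9 (Aim 1A-C) and Table 3, show it over a range such as r = .5 to .9, and say whether r refers to the latent propensity or to the observed yes/no values. In the Aim 1D paragraph, remove the description of the correlation as conservative for H1B unless those data support it.

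The new figure should come from the sponsor's estimate; the fitted values above should not be printed in its place. The cost is one rerun on data the sponsor should already hold, plus a few words. The stated detectable effect may become less favourable. The sample size stays at 216.
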